#### Radiotoxicity

Onset and duration of acute radiodermatitis is recorded due to the NCI-CTCAE criteria version 4.02. The “Late Effects of Normal Tissue – Subjective, Objective, Management, and Analytic scales” (LENT-SOMA) are applied at week 13 asking for ulcerations, telangiectasias, palpatory changes, retraction, atrophy, edema in the breast, lymph edema, and fibrosis [52]. The LENT-SOMA allows the quantification of late effects on normal tissue.

#### Physical fitness

All fitness measures are performed by trained study personnel at the Division of Preventive Oncology at the NCT.

*Muscle strength* is assessed by measuring isometric (4 positions) and isokinetic (2 angular velocities) muscle capacity with the IsoMed 2000® diagnostic module (isokinetic evaluation and training machine, D&R Ferstl GmbH, Hemau, Germany). The protocol includes testing of representative muscle groups for upper (shoulder rotators) and lower extremity (knee extensors and flexors). Reliability and validity of isokinetic dynamometer machines have been reported in several studies, with coefficients of variation below 10% [53-55].

*Endurance performance* (VO2peak) is measured on a bicycle ergometer (Ergostik, Geratherm Respiratory GmbH, Bad Kissingen, Germany) by performing a symptom-limited test with a step protocol (starting at 50 watt with steps of 25 watts every 2 minutes). The criteria of exhaustion is defined as achieved estimated maximum heart rate, plateau in VO2 and RQ >1.1. VO2peak is defined as highest 30-second average during the test. Peak workload, peak oxygen uptake and oxygen uptake at ventilatory threshold are taken for analysis. Cardiorespiratory exercise testing is well established in cancer patients and recommendations for testing procedures as well as safety guidelines in clinical trials with cancer populations have been defined [56]. The procedure is also used to exclude exercise-contraindicating cardiac impairments.

*Body composition* of the participants is measured with bioelectrical impedance analysis (BIA, Akern Srl, Pontassieve, Italy). This is a quick and non-invasive method, which determines the electrical impedance, or opposition to the flow of an electric current through body tissues to calculate an estimate of total body water, fat-free body mass and body fat [57]. BIA gives reliable measurements of body composition with minimal intra- and inter-observer variability in healthy volunteers [58]. In cancer patients during therapy, derived variables need to be interpreted with caution, e.g. due to potential lymphedema. In addition, algorithms used to calculate %fat mass might lead to biased values [59]. Thus, our focus will be on inter-individual changes with respect to the phase angle (reactance and resistance) during the intervention period rather than on absolute values or computed values for different compartments. In addition, body weight in light clothing, height, hip- and waist circumference are measured.

#### Biospecimen collection and biomarkers

Serum, plasma, and PBMCs are derived from whole peripheral blood samples, processed within 2 hours after taking the blood sample and stored at -80°C or cryopreserved in liquid nitrogen (PBMCs) for analyses of biomarkers after completion of the last study participant. Only CRP is directly analysed with nephelometry within the clinical routine lab.

Urine samples are collected for analyses of biomarkers of oxidative stress, i.e. urinary F2-isoprostane and 8-oxo-dG measured by chromatography-based methodology.

Saliva samples are collected with salivettes by the participants at 5 specific time points during a day (at waking, +0.5 h, noon, 5 pm, 10 pm/bed time) for analyses of diurnal cortisol slopes and cortisol morning peaks after study completion.

Immunological factors are assessed in fresh blood, including the quantity of FoxP3+ CD25+ regulatory T-cells and circulating lymphocytes subpopulations. In addition, in a subpopulation of n=40 participants (20 of each intervention arm) the specificity of FoxP3+ CD25+ regulatory T-cells is measured.

#### Safety issues

Potential adverse effects (e.g. lymphedema, pain, muscle soreness, nausea, dyspnea, tachycardia) are recorded by the participants at each training session by standardized questionnaires throughout the intervention period. Adverse events reported spontaneously by the patient or observed by physiotherapists, study nurse or physicians are recorded, e.g. sports accidents or injuries.

### Sample size

The primary aim is to compare changes on the overall fatigue scale from baseline to week 13 between the exercise and relaxation group. To detect a mean standardized effect size of 0.5 with a two-sided t-test with significance level 0.05 with a power of 80% a sample size of 80 breast cancer patients per arm is needed, 160 women in total, assuming a maximal drop-out rate of 20%. However, adjustment for the pre-intervention fatigue value in the regression models on post-intervention fatigue will lead to an improved power above 80% depending on the correlation between the pre- and post-intervention values [60].

This sample is also large enough to detect medium sized clinically relevant intervention effects on the secondary outcome EORTC QLQ-C30 subscales. Evidence-based guidelines for the interpretation of the clinical relevance of changes in the different EORTC QLQ-C30 subscales were recently published [48], categorizing difference between scores (on the 0-100 points scale) in trivial, small, medium, or large effect sizes. For example, effects are considered as medium size for differences of 19-29 in role function, differences of 14-22 in physical function, 11-15 in social function, 9-14 in cognitive function, and 13-19 for fatigue.

### Data analysis

The main intervention effect will be assessed on the basis of a comparison between exercisers and controls as defined at randomization, regardless of exercise adherence, i.e. according to the intent-to-treat principle. The differences in fatigue between groups will be assessed with a generalized estimating equation (GEE), which accounts for repeated observations on the same subjects over time. This method provides the most efficient estimate for the intervention effect in pretest-posttest trials [61]. Normality assumptions will be checked and data if necessary transformed. Imputation-based sensitivity analyses will be conducted to examine the potential effect of missing data on the results.

Similar analyses as for fatigue will also be performed for the secondary endpoints. In addition, analyses will be performed stratified by pre-treatment (e.g. neoadjuvant, adjuvant or no previous chemotherapy), to evaluate potential differential effects of the exercise intervention by pre-treatment. Further, subgroup effects of resistance training versus relaxation controls will be explored stratified by training adherence, changes in muscle strength, cardiorespiratory fitness, and body composition. Correlation analyses will be used to examine the relationship between changes of the various measured endpoints. Regression analyses regarding the repeated measurement design (T0, T1, T2, T3, T4, T5) will be applied to investigate the association between therapy modalities, cardiorespiratory fitness, muscle strength, and body composition and the different fatigue as well as QoL dimensions. The influence of other potential confounding factors, such as age, smoking, clinicopathologic characteristics, and comorbidities will be explored and accounted for in the analyses.

In addition, change in physical activity behavior post intervention will be explored for the follow-up time points using descriptive analysis.

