### Objectives

The primary objective of the BEST trial is to determine the effect of resistance training on fatigue compared to a relaxation control group among breast cancer patients during adjuvant radiotherapy.

Secondary objectives are to estimate the effects of the resistance training on quality of life, depression, cognitive function, and early and late radiotoxicity, as well as on physical fitness, including muscle strength, cardio-respiratory fitness, flexibility, and body composition. The effects of the resistance training on immunologic and inflammatory parameters and other biomarkers relevant to cancer prognosis will also be tested. Further, hypothesized biological mediators of physical activity and cancer-related fatigue will be explored and the relationships between cancer-related fatigue, physical fitness, and biomarkers of stress, inflammation, and immune function will be modelled. Safety and feasibility of progressive resistance training during radiotherapy will be evaluated, and the sustainability of the effects will be assessed.

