### Recruitment and randomization

All eligible breast cancer patients scheduled for adjuvant radiotherapy at the University of Heidelberg Medical Center are briefly informed about the BEST study during the therapy counselling visit (about 1-2 weeks before start of radiation). If interested, patients are then informed in detail by the BEST study physician and inclusion and exclusion criteria are verified. For each patient recruited into the study, written informed consent is essential prior to inclusion into the study after extensive information about the intent of the study, the study regimen, potential associated risks and side effects. The investigator will not undertake any diagnostic measures specifically required for the clinical trial until valid consent has been obtained. Upon written informed consent, the patient is scheduled for the baseline visit, which should be within 21 days prior to the start of radiation.

After completion of the baseline assessment and if the testing procedure does not indicate cardiovascular, respiratory or neurological problems that may contraindicate resistance training, the participant is randomly allocated to one of the two intervention groups. Allocation is done by the biometrician based on a predetermined list generated with a blocked randomization SAS procedure with a fixed block size, stratified by age (< 50 / ≥ 50 years of age) and baseline physical fatigue level (< 14 / ≥ 14). Stratification is used in the randomization process, as we anticipate these variables to have major influence on the outcome. To prevent possible bias, study personnel involved in the recruitment and the baseline assessment do not have access to the randomization lists and are not aware of the block size. Conversely, the biometrician does not have influence on the recruitment procedure.

Recruitment of n=160 patients started in February 2011 and was completed in March 2013.

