### Interventions

The begin of the training is the day of the first radiotherapy treatment. Patients participate in the intervention or control program for 60 minutes, twice weekly for 12 weeks. Participants train together with other cancer patients under supervision and guidance of experienced therapists. At days of radiation, participants frequently train directly before or after radiation due to logistic reasons. The physical status and well-being prior to and after a training session are recorded by the participant. The trainer documents attendance of each participant at each session. Similarly, if sessions have been missed, reasons are documented. In addition, for the resistance training individual weights and number of repetitions performed are documented.

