#### Relaxation intervention

Similar to the resistance training the relaxation intervention is performed for 60 minutes, twice weekly for 12 weeks in the exercise facility of the National Center for Tumor Diseases (NCT) in Heidelberg. It is based on the progressive muscle relaxation method according to Jacobson and does not include any aerobic or muscle strengthening components [37].

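### The planned between-arm contrasts within strata of adherence and of change in strength, fitness and body composition use post-randomisation stratifiers, so randomisation does not protect them and they should not be called subgroup effects

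*Protocol article*

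**What the plan says.** The Data analysis section first fixes the main comparison by randomised group, whatever the adherence. It then plans analyses by previous chemotherapy, which is a baseline factor. After that it adds that "subgroup effects of resistance training versus relaxation controls will be explored stratified by training adherence, changes in muscle strength, cardiorespiratory fitness, and body composition". The same section also plans correlations between changes in endpoints, repeated-measures regression of fatigue and quality of life on fitness, strength and body composition, and adjustment for potential confounders.

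The timing of the stratifiers is set elsewhere in the article:

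- **Randomisation.** Under Recruitment and randomization, once the baseline assessment is complete, "the participant is randomly allocated to one of the two intervention groups".
- **Training.** Under Interventions, "The begin of the training is the day of the first radiotherapy treatment".
- **Adherence.** Also under Interventions, "The trainer documents attendance of each participant at each session".
- **Changes.** In Table 2, strength and VO2peak are measured at T0 and next at T2; body composition is measured at T0, T1 and T2.
- **Expected effect of training.** The Objectives list effects of training "as well as on physical fitness, including muscle strength, cardio-respiratory fitness, flexibility, and body composition". The relaxation programme "does not include any aerobic or muscle strengthening components".

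**The concern.** A subgroup effect is a comparison of randomised arms among patients defined by something that the allocation cannot have altered. Previous chemotherapy meets that condition. Adherence and the three changes do not, yet they follow it in the same language.

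Three separate problems arise.

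- **Selection.** A relaxation patient whose strength rose did so without strength training. An exerciser in the same stratum may have got there because of it. The two are likely to differ in recovery, motivation or activity outside the trial, and any of these may also bear on fatigue.
- **Blocked effect.** If training reduces fatigue partly by raising strength, comparing arms among patients with similar strength change takes out some of that effect.
- **Non-comparable adherence.** Attending resistance sessions and attending relaxation sessions are different behaviours, so adherent patients in the two arms need not be alike.

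What is at stake is the reading of these exploratory results: an apparent difference in a stratum could arise without any effect of training on fatigue, and a real effect could be masked.

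**Working it through.** **1. The plan's own figure.** Sample size section: standardised effect 0.5, two-sided 5% t-test, 80% power, 20% drop-out. The t-test needs 63.8, so 64 evaluable per arm, and 64 / (1 − 0.20) = 80 per arm. The stated 80 per arm (160 in total) reproduces, and nothing below changes it.

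**2. Are the stratifiers post-randomisation?** The order is baseline visit, allocation, first training session on the first radiotherapy day, attendance recorded at each session, then T1 and T2 measurements. Attendance and every change score therefore come after allocation. The primary endpoint is fatigue change to week 13, which is T2. Strength and VO2peak are not measured at T1, so their changes over the intervention coincide with the fatigue change and do not precede it.

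**3. Size of the bias with no true effect.** The inputs are assumptions; the document gives none of them:

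- d = shift in strength change caused by training: 0.5 to 1.0 SD
- r = within-arm correlation of strength gain with fatigue improvement, from shared causes: 0.2 to 0.4
- both changes normal with SD 1, equal arms, strata split at the pooled median, which lies at d/2
- fatigue change independent of arm; lower is better

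In the high-change stratum, exercisers need a residual strength gain above −d/2 and controls one above +d/2. Their mean residual gains are φ(d/2)/Φ(d/2) and φ(d/2)/[1 − Φ(d/2)]. Multiplying by −r gives mean fatigue change, so exercise minus relaxation is

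r × φ(d/2) × {1/[1 − Φ(d/2)] − 1/Φ(d/2)}.

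By symmetry the low-change stratum gives the same value.

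| d | φ(d/2) | Φ(d/2) | multiplier of r | r = 0.2 | r = 0.4 |
|---|---|---|---|---|---|
| 0.5 | 0.387 | 0.599 | 0.318 | 0.06 | 0.13 |
| 1.0 | 0.352 | 0.691 | 0.632 | 0.13 | 0.25 |

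All values are positive, that is, against training. At r = 0 the difference is zero.

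**4. A real effect.** In a simulation with a true effect of −0.5 SD that does not run through strength, and d of 0.5 to 1.0, the within-stratum estimate shrinks to between −0.41 and −0.31 at r = 0.3, and to between −0.34 and −0.18 at r = 0.5. Any effect that did run through strength would be a further loss.

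**5. Error rate at trial size.** With 64 evaluable per arm, no true effect and r of 0.3 to 0.5, the nominal 5% test in the high-change stratum rejected in about 6% to 23% of simulated trials. The lower end is barely above nominal.

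**6. A different contrast, which the text does not specify.** Suppose the best-adhering share q of exercisers were set against all controls, with r now the within-arm correlation of adherence with fatigue improvement. The spurious difference is −r × φ(z)/q, where z cuts off the top q.

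- q = 0.7: φ(z)/q = 0.348/0.7 = 0.497, giving −0.10 (r = 0.2) to −0.20 (r = 0.4)
- q = 0.5: φ(z)/q = 0.399/0.5 = 0.798, giving −0.16 to −0.32

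These favour training, the opposite direction to step 3.

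**The case against.** The strongest reply is containment. The main comparison is by intention to treat, secondary endpoints are to be analysed similarly, and the disputed strata are only to be explored. That stands, and it limits the consequence to interpretation. It does not remove the bias, because an exploratory label tempers the strength of a claim and does not make the compared groups alike.

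A second reply is that confounders will be accounted for. Those named (age, smoking, clinicopathologic characteristics, comorbidities) need not capture recovery or motivation, and adjusting for them restores neither randomisation nor the part of the effect taken out by stratifying.

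A third is that one sentence in an article cannot show cut-points, which arms are stratified or what method is used. That also stands: leaving out such detail is no fault, and only the stated between-arm contrast is criticised here.

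Three stronger readings are tempting and are not supported.

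- A reader might infer that mechanism rests on correlations alone, since "Correlation analyses will be used to examine the relationship between changes of the various measured endpoints". The section also plans repeated-measures regression with confounder adjustment, and the Objectives say the relationships will be modelled.
- A reader might take the strata as the trial's mediation or dose-response analysis. The Objectives say that "hypothesized biological mediators of physical activity and cancer-related fatigue will be explored", but biomarkers are not among the stratifiers, and dose-response is not a stated aim.
- A reader might conclude that the plan as written can bias results in either direction by a known amount. In the illustration, contrasts within strata err only against training. The favourable figures belong to the contrast in step 6, and all the sizes are assumed.

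**Conclusion.** The point holds for the strata sentence. It plans comparisons between arms within groups formed by adherence and by changes after allocation, and calls them subgroup effects. Randomisation does not protect these comparisons, and stratifying on the changes takes out effect that runs through them.

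The illustrative bias is about 0.06 to 0.25 SD against training within strata, compared with the 0.5 SD design effect. It rests on the assumed shift and correlation and on a median split. It vanishes when there is no effect and nothing links the stratifier with fatigue, which is unlikely here, but neither its size nor its sign is certain in practice. The primary result, the sample size and the analysis by previous chemotherapy are unaffected. It should be corrected, but it does not endanger the trial's main conclusion.

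**What to change.** - Keep the term subgroup effect for baseline factors such as previous chemotherapy, baseline strength or baseline VO2peak, and test each with an arm-by-factor interaction.
- Replace the between-arm contrasts within adherence and change strata in one of two ways. Either report them as associations labelled non-randomised, or use a mediation, complier-average or principal-stratification analysis with its assumptions stated. For mediation these include no unmeasured confounding of mediator and outcome; adjusting for arm, baseline fatigue and baseline covariates does not guarantee that.
- State that strength and VO2peak changes coincide with T2 fatigue, because neither is measured at T1. Placing the mediator before the outcome is possible only for measures taken at T1, such as body composition and the biomarkers.

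The cost is modest extra programming and more cautious wording of these exploratory results. No new data are needed.

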## Discussion

The BEST study will add to current knowledge about exercise in breast cancer patients with respect to several novel aspects being tested: (1) Exercise performed in parallel to radiotherapy; (2) progressive resistance training; (3) exercise effect beyond psychosocial training effects; (4) effects on immune function, and (5) sustainability and long-term effects of a 12-week exercise intervention.

Among breast cancer patients receiving radiotherapy the most frequently reported side effect is fatigue. As about 72.000 women in Germany are newly diagnosed with breast cancer each year [62], the majority receiving radiotherapy, this radiation-related fatigue is a substantial health problem. Exercise may be an effective treatment against fatigue. Thus, it is surprising that exercise during radiotherapy has been minimally investigated in breast cancer patients so far. To our knowledge, only five randomized exercise trials included breast cancer patients during adjuvant radiotherapy [63-67]. Three of these studies included also patients during other adjuvant treatments (chemotherapy, hormone therapy) [64,66,67] and one was a pilot study including also prostate cancer patients [65], leaving only one exercise study with only breast cancer patients during adjuvant radiotherapy but with a small sample size of only n=46 [63].

Radiation can be muscle damaging (myotoxic), resulting in significant reductions in skeletal muscle mass and function [68]. Resistance training can counteract this muscle degradation. The negative influence of cancer therapy is a major rationale to investigate the effect of resistance exercise during adjuvant radiotherapy, as training in parallel to adjuvant treatment might prevent or mitigate treatment side effects such as fatigue.

Previous randomized exercise trials mostly investigated aerobic exercise, but benefits of resistance training in cancer patients and survivors on quality of life and fatigue have also been reported [15,69-71]. To our knowledge, only seven studies investigated pure resistance training in cancer patients and survivors [69,72-77]. Among those studies, two had insufficient power (n=22 and 38) [76,77] and of the others only three focused on breast cancer patients [69,72,75]. However, no randomized controlled trial investigated progressive resistance training in breast cancer patients during adjuvant radiotherapy.

A further strength of the BEST study is the choice of the control group, i.e. of a standardized relaxation training without any aerobic or resistance exercise components, but which reflects the training schedule and psychosocial conditions of the exercise intervention. Positive psychosocial “side effects” of group-based exercise training have been observed [78], which potentially can contribute to a lower perception of fatigue and higher QoL, in addition to physiological effects of the exercise on fatigue. Thus, the BEST design enables us to discern the “pure” physiological effects of exercise beyond potential psychosocial effects of a group-based training, which are related to social interactions, group support, improved self-efficacy, or attention by the trainer. Psychosocial and behavioural interventions have also shown some beneficial effects regarding fatigue and QoL [79,80]. Thus, it is still unclear, to what extent the observed benefits of exercise interventions are really caused by physical training, because previous studies have commonly used a “usual care” control group.

Further, the pathophysiology of fatigue and the mode of action of exercise on its prevention and treatment are not well understood. Our trial enables investigation of the effects of resistance training on immunologic parameters as well as on biomarkers of inflammation, oxidative stress, and diurnal cortisol slopes. While the intervention effect on fatigue and potential underlying biological mediators is one focus of the trial, another focus is the examination of the effects of resistance exercise on prognostic factors and health-relevant biomarkers. Especially regulatory T-cells will be investigated in detail, as those have been found to be associated with prognosis in breast cancer patients [31-33].

Finally, in case of the detection of beneficial effects during or at the end of an exercise intervention, it is of interest whether those benefits sustain over a longer period of time. To-date, data on the sustainability of exercise interventions is limited. Therefore, we follow the BEST participants over one year post-intervention and assess at 3 post-intervention time-points fatigue, QoL, physical fitness, and their physical activity behavior.

In summary, the BEST study shall contribute to a better understanding of the physiological and psychological effects of resistance training and their biological and immunological mechanisms in breast cancer patients during adjuvant radiotherapy. The ultimate goal is the implementation of an optimized intervention program to reduce fatigue and improve quality of life and potentially the prognosis after breast cancer.

